#### Scales to measure autistic symptoms

Social Communication Questionnaire for Adults with Intellectual Disability (SCQ-AID) (47): The SCQ is a caregiver-rated dimensional measure of ASD symptom severity. The SCQ-AID is an adaptive version to improve the utility of the SCQ for adults with IDD. This newly developed algorithm has 24 items compared with the 40 items in the original instrument. <15 minutes to complete.

#### Scales to measure cognitive function

NIH Toolbox® Cognition Battery (NIHTB-CB): The NIHTB-CB is an iPad-based battery of brief memory, executive function, processing speed, and language tests, which was developed within the NIH Blueprint for Neuroscience Research. The NIHTB-CB has the potential to provide a highly standardized, objective, and scalable tool for use across laboratories and clinical trial sites and has been shown as a good candidate outcome measure to examine broad nonverbal cognitive changes for individuals with IDD (valid and reliable for those with a mental age of  $\geq 5$  years; implementable for those with a mental age of  $\geq 3$  years) (42). The NIHTB-CB will be used to monitor the change in cognitive performance pre-and post-treatment of nabilone. To allow for accurate scoring based on the established norm, the administration of NIHTB-CB will collect a set of limited personal identification information, including sex, age, and education level, plus study ID. This assessment will be delivered on-site at pre-treatment (V 0), post-treatment (V 1), and safety follow-up (V-F). It takes approximately 60 minutes to complete each full assessment. It should be noted that this administration time is approximate considering the different levels of motivation and cooperativeness in participants. The norming version for neurotypical people aged 3-85 years is intended to be administered with a 30-minute duration (48).

#### Scale to measure adaptive function

Adaptive Behavior Assessment System-III (ABAS-3), Adult Form. The ABAS-3 is a measure of adaptive behaviour that has been validated in a number of psychiatric populations and has been used to assess functioning in neurodevelopmental disabilities (49). It provides an overall composite score of adaptive functioning, including subscores indexing social skills, conceptual and practical skills. Approximately 20 minutes to complete.

#### Scale to measure behavioural problems

1. Aberrant Behavioral Checklist-Irritability subscale (ABC-I): The ABC is a 58-item rating scale completed by a caregiver. It consists of 5 subscales. Among them, the Irritability subscale consists of 15 items. The ABC was empirically derived to assess treatment effects, and it has sound psychometric characteristics (50). Caregivers were asked to consider the participant's behaviour over the last four weeks at Screen/Baseline. Here we will only employ the ABC-I to confirm eligibility (presence of tantrums, aggression, self-injury) and to assess treatment effects (41). <10 minutes to complete.
2. Modified Overt Aggression Scale (MOAS): The MOAS (51) is a reliable measure used to measure behavioural problems in adults with IDD. It consisted of 4 items and is administered

by the researcher's interview with the caregiver. It was used as the primary outcome in one of the largest RCT on aggression in this population (52). <5 minutes to complete.

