| Acceptability Evaluation |  |   |  |   |   | • | Either or |

Abbreviation: Dx = diagnosis; MacCAT-CR = MacArthur Competence Assessment Tool for Clinical Research; Moss-PAS (ID) = Moss Psychiatric Assessment Schedules; ABAS-3 = Adaptive Behavior Assessment System, Third Edition; PE = physical examination; AE = adverse event and severe adverse event; NIH-Toolbox = NIH Toolbox® Cognition Battery; ABC-I = Aberrant Behavior Checklist-Irritability Subscale; MOAS = Modified Overt Aggression Scale; CGI-I = Clinical Global Impressions (CGI) scale-Improvement; CGI-S = Clinical Global Impressions (CGI) scale-Severity; Anxiety-ADAMS = General Anxiety Subscale of Anxiety, Depression, and Mood Scale; Stress-DASS-21 = Stress Subscale of the short-form version of Depression Anxiety Stress Scales; BFDS = Brief Family Distress Scale; SCQ-AIQ = Social Communication Questionnaire for Adults with Intellectual Disability.

a: Either in-person or virtual visit

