### Elective Virtual Assessment

To reduce barriers associated with traffic and time and to future-proof the research protocol in case of another COVID lockdown, we will provide the option for virtual assessments. As shown in the last column of Table 1, interviews that collect data on demographics, clinical history, diagnoses alongside medication use, competence, and adverse effects can be conducted virtually using teleconferencing/videoconferencing software (Webex). Additionally, a blank paper copy of outcome measures rated by caregivers (including the ABC-I, MOAS, Anxiety-ADAMS, Stress-DASS-21, BFDS, and SCQ-AIQ) can be electively sent to them via mail. Completed questionnaires can be mailed, faxed, scanned, or photographed back to the study team. If the caregivers choose to send the completed questionnaire by mail, we will provide a pre-paid postage envelope.

The virtual sessions will be undertaken in coordination with in-person sessions based on the same research standards. The participants and caregivers can flexibly choose either the in-person or virtual assessments for those elective options (Table 1). We will notify both the participant and their caregiver of this virtual option when explaining the study (based on the Telephone Contact Script) and discussing the informed consent.

If the participant/SDM/caregiver chooses to have a virtual informed consent process (as detailed in Section 5) and virtual screening assessment, we will only start the assessment after we receive

the signed informed consent form (with wet signatures). To reduce the barriers by enhancing the convenience and flexibility of participants/caregivers, if they choose to have screening assessments done virtually, the measures of the Screening Visit which require in-person assessments (i.e., pregnancy test, height, vital signs and physical examination) will be carried out in combination with those implemented during the pre-treatment assessment (V 0).

During virtual visits, the study team will document the records of virtual assessment on a study computer and sign the documents with e-signature first when working remotely. Then the person(s) who implements the virtual assessment will then print out the e-signed records and add a wet signature to verify the sources at first available opportunity on-site.

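### The MOAS is a researcher interview in Section 3.4 but a returnable paper form in Section 3.2, and nothing keeps one mode across V 0 and V 1

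*Protocol*

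**What the plan says.** Protocol Section 3.4 (Scale to measure behavioural problems) describes the MOAS as a four-item scale administered "by the researcher's interview with the caregiver", taking less than five minutes.

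Protocol Section 3.2 (Elective Virtual Assessment) describes another route: "a blank paper copy of outcome measures rated by caregivers (including the ABC-I, MOAS, Anxiety-ADAMS, Stress-DASS-21, BFDS, and SCQ-AIQ) can be electively sent" to caregivers. It continues: "Completed questionnaires can be mailed, faxed, scanned, or photographed back to the study team". On who decides: "The participants and caregivers can flexibly choose either the in-person or virtual assessments for those elective options".

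Table 1 schedules the MOAS at V 0 and V 1 and leaves the visit type open, which its footnote defines as "Either in-person or virtual visit". The lists of assessments in Sections 3.1 and 3.2 treat the MOAS as reported or rated by the caregiver and do not mention an interviewer.

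Section 3.1 names the ABC-I and MOAS together as the principal measures of change in severe behavioural problems. Table 1 puts the ABC-I as primary and the MOAS as secondary among clinical-effect outcomes, all within the exploratory objective. Section 8 analyses pre/post behavioural change by paired t test in a single arm.

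**The concern.** Staff who follow Section 3.4 and staff who follow Section 3.2 would collect the MOAS in different ways. An interviewer can probe, clarify and score to a common standard. A caregiver alone with a form cannot be guided in that way, so the two modes may give different scores for the same behaviour.

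A paired comparison relies on measuring the same way twice. If a caregiver is interviewed at V 0 and fills in a form at V 1, or the reverse, any difference between modes goes into that participant's change score. With no control arm, nothing cancels it. The estimate at stake is one that the protocol says will inform the follow-up randomised trials.

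**Working it through.** **Can the two sections be read together?** One might take the paper copy as an aid to a telephone interview. Section 3.2 does not read that way. It first lists what can be done as virtual interviews (demographics, clinical history, diagnoses and medication use, competence, adverse effects), and the MOAS is absent. It then lists the paper measures, and the MOAS is present. No interviewer step is described between sending the form and its return. The two sections conflict.

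**Is the mode fixed within a participant?** The only safeguard is general: "The virtual sessions will be undertaken in coordination with in-person sessions based on the same research standards". It does not require the same mode at both visits.

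**The plan's own figure.** Inputs from Section 8: 40 enrolled, 25% attrition, so 40 × (1 − 0.25) = 30; two-sided alpha 0.05; power 0.80; detectable d = 0.53. For a paired t test with 29 degrees of freedom and noncentrality d × √30, power at d = 0.53 is 0.801 and the smallest detectable d is 0.529. The stated figure reproduces.

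**Illustration of the mode effect.** The protocol gives neither of the two quantities needed, so both are assumptions:

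- f, the share of participants switching mode in one direction, with none the other way: 25% or 50%.
- m, the mode difference in SD of the change score: 0.2, 0.3 or 0.5.

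With no true change, and switching unrelated to outcome, the bias in mean change is f × m and the variance becomes 1 + m² × f × (1 − f). The rejection rate comes from the same noncentral t with noncentrality √30 × f × m / √(variance).

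| m | f | Bias (SD) | Rejection rate, n = 30 |
|---|---|---|---|
| 0 | any | 0 | 5% |
| 0.2 | 25% | 0.05 | 5.8% |
| 0.2 | 50% | 0.10 | 8.2% |
| 0.3 | 25% | 0.075 | 6.8% |
| 0.3 | 50% | 0.15 | 12.3% |
| 0.5 | 25% | 0.125 | 9.9% |
| 0.5 | 50% | 0.25 | 25.0% |

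In the last row the variance is 1 + 0.25 × 0.25 = 1.0625, so the standardised bias is 0.25 / 1.031 = 0.243. The raw bias is 0.25 / 0.53 = 47% of the detectable effect.

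**Balanced switching.** If 25% switch each way with m = 0.5, the shifts cancel and the bias is zero. The variance becomes 1 + 2 × 0.25 × 0.25 = 1.125. A true effect of 0.53 is then seen as 0.53 / √1.125 = 0.50, and power at 0.50 with n = 30 is about 0.75 instead of 0.80. This is noise, and modest.

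**The case against.** The case against giving this much weight is substantial, and most of it stands.

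- **Standing of the measure.** MOAS change serves only the exploratory objective, and Table 1 ranks it below the ABC-I. Tolerability and safety do not depend on it. This limits the importance of the point.
- **Likelihood of switching.** V 0 and V 1 both include in-person items (vital signs, weight, NIH Toolbox, drug pick-up), and Section 3.1 places V 1 on site. A five-minute interview fits into either visit. Switching may be rare, but the text does not require the interview to take place there.
- **Size.** A reader might infer from the table that the design carries a type I error of up to 25%. The documents do not support that. It needs a systematic mode difference together with a net one-way switch, and neither is documented. Zero bias is equally compatible with the text.
- **Attribution.** In an open-label single-arm study of people selected for high ABC-I scores, expectancy and regression to the mean remain whatever the mode. Holding the mode constant would not make the change attributable to nabilone. It removes one avoidable contributor.
- **Late forms.** A reader might also infer that V 1 forms will be completed after the taper has begun. Table 1 places the MOAS at V 1 and the taper follows that visit. The protocol is silent on completion dates, and silence alone does not establish this.
- **Other scales.** It is tempting to extend the point to every caregiver scale, or to a same-informant rule. The demonstrated conflict concerns the MOAS alone. Section 3.4 describes the ABC-I, for example, as completed by a caregiver, which fits a paper form.

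None of this removes the conflict between Sections 3.2 and 3.4.

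**Conclusion.** The protocol gives two incompatible ways of administering the MOAS and does not hold the mode constant between the two visits whose difference is tested. The consequence is possible noise in the mean change. Bias follows only if the modes differ systematically and switching is net one-directional.

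Under the assumed range, bias runs from zero to about 0.25 SD of change, and the rejection rate from the nominal 5% to about 25% at n = 30. These figures show what could happen; they do not estimate what will. The stated n = 30 and d = 0.53 are correct and need no change. The primary objective is unaffected. The point deserves action because it concerns how data are collected: analysis cannot restore comparability afterwards, and the text does not ask for the mode to be recorded.

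**What to change.** In Section 3.2 (Elective Virtual Assessment), remove the MOAS from the paper measures and add it to the interviews that may be held virtually. In Section 3.4, state that the MOAS is administered by researcher interview at both V 0 and V 1, in person or by phone or video when the assessment is virtual. Add a note to the MOAS row of Table 1 to the same effect, and record the mode used at each visit.

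The cost is a few lines of wording and one extra data field. Families lose a little flexibility, since the caregiver must be available for an interview of under five minutes. Section 3.2 already provides for teleconferencing and videoconferencing, so virtual participation is kept.

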#### Scale to measure anxiety

General Anxiety Subscale of the Anxiety, Depression, and Mood Scale (ADAMS): The ADAMS (53) is an informant-report instrument specifically developed for adults with IDD, consisting of five subscales. Herein, we will only use the General anxiety subscale, which consists of seven items that cover five of the diagnostic criteria or symptoms of anxiety. The score on the General anxiety subscale ranges from 0 to 21. <5 minutes to complete.

#### Scales to measure overall clinical impression

Clinical Global Impressions (CGI) scale: The CGI is a well-established research rating tool to provide a brief, stand-alone assessment of the clinician's view of the patient's global functioning prior to and after initiating a study medication (54). The CGI-Severity (CGI-S) asks the clinician one question: "Considering your total clinical experience with this particular population, how mentally ill is the patient at this time?" which is rated on the following seven-point scale: 1=normal, not at all ill; 2=borderline mentally ill; 3=mildly ill; 4=moderately ill; 5=markedly ill; 6=severely ill; 7=among the most extremely ill patients. This rating is based upon the average severity of observed and reported symptoms, behaviour, and function in the past seven days. The CGI-Improvement (CGI-I) is for the clinician to compare the patient's overall clinical condition to the baseline visit and is rated on a seven-point scale: "Compared to the patient's condition at admission to the project [prior to medication initiation], this patient's condition is: 1=very much improved since the initiation of treatment; 2=much improved; 3=minimally improved; 4=no change from baseline (the initiation of treatment); 5=minimally worse; 6= much worse; 7=very much worse since the initiation of treatment." <5 minutes to complete.

#### Scales to assess capacity to make informed consent

MacArthur Competence Assessment Tool for Clinical Research (MacCAT-CR): The MacCAT-CR (44) provides a structured format for capacity assessment. Beginning with project-specific disclosures to potential participants, the MacCAT-CR measures the four generally accepted components of decision-making competence: understanding, appreciation, reasoning, and the ability to express a choice. The informed consent of the participants who fail to pass this assessment will be completed by their substitute decision maker. Herein, a score of 70% or higher in the MacCAT-CR will indicate that a given participant is deemed competent to consent. This cutoff is borrowed from the protocol of an ongoing Brain Canada-funded study on elderly with dementia - "Standardizing Care for Neuropsychiatric Symptoms and Quality of Life in Dementia". This cutoff of 70% is in-between the cut-offs used for schizophrenic adults (55) and neurotypical children (56), which we deem a middle ground to balance sensitivity and specificity of assessing capacity to consent. This should take approximately 15 minutes to complete.

In addition to using the MacCAT-CR scale, the research team will also utilize clinical assessment of the potential participants to determine their capacity to consent to participating in the research, in a similar manner to determining capacity for clinical treatments as outlined in clinical guidelines (45). During the research consent conversation, the research team member will look for evidence of the same four components of decision-making capacity. Specifically, research team members will use their clinical expertise and judgement to check that participants: (a) have an understanding

of what participating in this study entails and the associated benefits and risks; (b) have an appreciation for the how these benefits and risks apply to them specifically; (c) are able to show reasoning that their decision to participate aligns with their values; and (d) are able to communicate their choice to the research team. If during the consent conversation, the person obtaining consent finds, based on their clinical judgement, that any of these criteria are not found to be met, consent will have to be obtained by from the substitute decision maker.

#### Scales to assess adverse events related to the study medication

UKU side effect rating scale: The UKU side effect rating scale is a short and easy-to-use instrument that captures the core dimensions of side effects in patients using psychotropic medications. The UKU side effect rating scale is widely used in both research and in clinical settings (57), and is delivered by interviewing and observing the patients and their caregivers. Herein, we will adopt the UKU side effect rating scale specifically adjusted to adults with IDD, which consists of 35 items out of the original 48 items. This revised checklist seems more feasible to observe items that are concrete and objective than items based on the patients' subjective experiences (58). Approximately 20 minutes to complete.

#### Scales to measure caregiver's stress and crisis

1. The Stress subscale of Depression Anxiety Stress Scales (DASS-21): The 7-item Stress subscale of the original DASS-21 (59) is used to assess perceived feelings of parent stress. Items measure feelings experienced over the previous week and are scored on a 4-point Likert scale from 0 ("did not apply to me at all") to 3 ("applied to me very much, or most of the time"), providing total scores between 0 and 21 for stress. <5 minutes to complete
2. Brief Family Distress Scale (BFDS): The BFDS (60) measures the subjective experience of crisis in families of people with neurodevelopmental disabilities. This measure is meant to assess the experience from the caregiver's perspective and is placed along a continuum of distress, from mild stress to qualitatively distinct and immediate periods of crisis. <1 minute to complete.

#### Scales to measure acceptability

Custom-designed acceptability questionnaire: This questionnaire is similar to that used in (23), which inquires the acceptability of all study components, including recruitment, withdrawal rate, study visit attendance, protocol adherence and the time burden of completing questionnaires.

#### Other measures

1. Demographic questionnaire
2. Current and Concomitant medications (including type, dose, and duration of treatment)\*
3. Height
4. Weight
5. Vital signs (blood pressure, heart rate, and temperature)
6. Drug diary to evaluate compliance

---

\*The high dose of benzodiazepine (more than the benzodiazepine equivalent to lorazepam 2 mg daily) and other cannabinoids, which are still used 4 weeks before the start of the use of the study drug (titration phase), are not permitted. Other concurrent medications and non-medication treatments (including behavioural therapy, psychological therapy, occupational therapy, support group etc.) are permitted before and during the trial.

### MR Imaging

MRI scans are optional and exploratory, dependent on the participants' capacity to comply with the procedures and the participants' and caregivers' willingness to participate. If the caregiver, substitute decision maker (SDM), and participants are willing and capable to receive the MRI assessment, they will receive an instruction using a custom-built social script, which comprises a series of photographs of the research procedures, environments, and files of the sounds emitted by MRI to help participants be acquainted with the scanning environment and learn the procedures at the screening visit (S-V). The visit of MRI assessments can be arranged either on the same day with the baseline assessment (V 0) or the other day before the start of the dose titration phase.

For the MRI measure, we will use the CAMH research-dedicated 3 Tesla MRI scanner, operated by a well-organized team including a full-time MR physicist and research technologist. The acquisitions we will obtain include a T1-weighted, a naturalistic film viewing fMRI, and proton magnetic resonance spectroscopy ( $^1\text{H}$  MRS) scans. The entire MR scan session will take approximately 30 minutes.

The acquisition details are as follows.

T1: A standard high-resolution T1-weighted scan will be acquired, as needed for processing both the fMRI and MRS data. Approximately 4.5 minutes to complete.

fMRI: High spatial and temporal resolution multiband EPI fMRI scans are acquired to examine functional activity. The task paradigm is using naturalistic film viewing, which will take place in the scanner. All participants are instructed to passively view the films and pay attention to the cinematic events. The negative-valence emotion clip is presented to the participants. The display of a film is preceded and followed by an epoch during which the participants passively gazed at an all-black slide. The duration of this epoch is 30 seconds (61). The naturalistic film stimuli are intentionally adopted as the paradigm for its ecologically valid nature. They approximate real life scenarios, which can elicit dynamic emotion responses and facilitate better participants' compliance in the scanner at the same time (62). The fear emotion clip is selected, as the negative emotion valence modulation is associated with the effect of THC on emotion regulation (20). Approximately 5 minutes to complete.

$^1\text{H}$  MRS: A spectroscopy scan is based on the MESHcher-GARwood Point RESolved Spectroscopy (MEGA-PRESS) sequence. The neurochemical profile is extracted from the anterior cingulate cortex set as the volume of interest, according to our established parameters.

The cannabinoids help regulate excitatory glutamate (E) and inhibitory  $\gamma$ -aminobutyric acid (GABA) (I) transmission (13). Thus, we aim to use  $^1\text{H}$  MRS to measure glutamate and GABA metabolite. The anterior cingulate cortex is chosen as the region of interest as it has a high CB1 concentration (20), and is critically involved in emotional regulation. Approximately 15 minutes to complete.

